## Abstract

**Background:**

Most patients presenting to US Emergency Departments (ED) with chest pain are hospitalized for comprehensive testing. These evaluations cost the US health system >$10 billion annually, but have a diagnostic yield for acute coronary syndrome (ACS) of <10%. The history/ECG/age/risk factors/troponin (HEART) Pathway is an accelerated diagnostic protocol (ADP), designed to improve care for patients with acute chest pain by identifying patients for early ED discharge. Prior efficacy studies demonstrate that the HEART Pathway safely reduces cardiac testing, while maintaining an acceptably low adverse event rate.

**Objective:**

The purpose of this study is to determine the effectiveness of HEART Pathway ADP implementation within a health system.

**Methods:**

This controlled before-after study will accrue adult patients with acute chest pain, but without ST-segment elevation myocardial infarction on electrocardiogram for two years and is expected to include approximately 10,000 patients. Outcomes measures include hospitalization rate, objective cardiac testing rates (stress testing and angiography), length of stay, and rates of recurrent cardiac care for participants.

**Results:**

In pilot data, the HEART Pathway decreased hospitalizations by 21%, decreased hospital length (median of 12 hour reduction), without increasing adverse events or recurrent care. At the writing of this paper, data has been collected on >5000 patient encounters. The HEART Pathway has been fully integrated into health system electronic medical records, providing real-time decision support to our providers.

**Conclusions:**

We hypothesize that the HEART Pathway will safely reduce healthcare utilization. This study could provide a model for delivering high-value care to the 8-10 million US ED patients with acute chest pain each year.

**ClinicalTrial:**

Clinicaltrials.gov NCT02056964; https://clinicaltrials.gov/ct2/show/NCT02056964 (Archived by WebCite at http://www.webcitation.org/6ccajsgyu)

## Introduction

### Background

Current care patterns for acute chest pain fail to focus health system resources, such as hospitalization and cardiac testing, on patients most likely to benefit. Each year, approximately 8-10 million patients complaining of chest pain present to an Emergency Department (ED) in the United States [1]. To avoid missing acute coronary syndrome (ACS), ED providers liberally hospitalize patients with acute chest pain for comprehensive cardiac evaluations (serial cardiac biomarkers and stress testing or angiography). However, <10% of these patients are ultimately diagnosed with ACS [2-6], and this pervasive overtesting costs an estimated US $10-13 billion annually [5,7]. Current guidelines for the management of suspected ACS recommend provocative or anatomic testing as a default strategy, serving to reinforce this overtesting behavior [7].

The Chronic Care Model, as adopted from Wagner’s work, identifies the use of evidence-based clinical decision support (CDS) systems as a way to address health system needs and improve health care delivery in chronic conditions such as cardiovascular disease [8-11]. Consistent with this model, accurate ACS risk stratification care pathways are designed to eliminate unnecessary testing and improve quality of care by decreasing false-positive results, nondiagnostic testing, exposure to radiation, and excess costs [12]. The history/ECG/age/risk factors/troponin (HEART) Pathway is an accelerated diagnostic protocol (ADP), which combines a clinical decision aid (the HEART score; Table 1) [13-15], with 2 serial troponin measurements, to identify patients with chest pain who can safely be discharged without objective cardiac testing (stress testing or angiography), either urgently or during follow-up care. Prior studies have established that use of the HEART Pathway reduces cardiac testing by >20%, while maintaining an acceptably low adverse event rate [15-17]. What is needed now is a rigorous evaluation of the implementation of the HEART Pathway into *real-world* clinical settings to determine its effectiveness.

**Table 1 table1:** The HEART score.

Category	Description	Points
History	Highly suspicious	2
	Moderately suspicious	1
	Slightly suspicious	0
ECG	Significant ST-depression	2
	Nonspecific repolarization abnormality	1
	Normal	0
Age	>65	2
	45-65	1
	<45	0
Risk Factors	3 or more risk factors	2
	1-2 risk factors	1
	No risk factors	0
Troponin	>3x normal limit	2
	1-3x normal limit	1
	<normal limit	0
Total		

### Objectives and Hypotheses

In this paper, we describe the rationale and methods utilized to test the effectiveness of the HEART Pathway ADP within a health system consisting of three diverse hospital settings. We hypothesize that implementation of the HEART Pathway will significantly reduce hospitalizations and the rate of objective cardiac testing among low-risk patients, without increasing adverse cardiac events.

## Methods

### Study Design

This prospective pre-post interrupted time series design compares the risk stratification of patients with acute chest pain before and after implementation of the HEART Pathway ADP. Wake Forest Baptist Health is a three-hospital academic health system located in the Piedmont Region of North Carolina. It consists of a large quaternary academic medical center with approximately 104,000 ED visits annually, a small community hospital with an annual ED volume of about 37,000 patients, and a free standing ED in an adjacent rural county with approximately 12,000 annual ED visits. This study is approved by the Internal Review Board of the sponsoring organization and is registered with clinicaltrials.gov (NCT02056964).

### Eligibility

The target population is adult patients with acute chest pain, in which the provider is concerned about possible ACS, but does not have evidence of an ST-segment elevation myocardial infarction (STEMI) on electrocardiogram (ECG). Therefore, adult patients (aged ≥ 21 years) with acute chest pain, provider-ordered troponins, and without STEMI will be included. Based on STEMI rates at Wake Forest Baptist Health, we expect <5% of patients with acute chest pain to be excluded due to ECG criteria.

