### HEART Pathway Implementation

The HEART Pathway intervention will incorporate elements of the Chronic Care Model framework (decision support and clinical information systems) by providing test ordering and disposition decision support to ED practitioners and personalized care planning for patients with acute chest pain [8,18,19]. This intervention uses a clinical decision aid (the HEART score; Table 1) [13-15], with 2 serial troponin measurements obtained at 0 and 3 hours after ED presentation. The HEART Pathway algorithm (Figure 2) will be integrated into the EMR system, EPIC (Madison, WI, USA), as an interactive CDS tool. A model window (on-screen pop-up) will display the HEART Pathway tool as a Best Practice Advisory when clinically indicated. The child window will require interaction before the user may return to the parent window in the EMR, but will not force the user to utilize the HEART Pathway tool (the alert will be presented as a *soft-stop*). The modal window will appear when a provider has ordered a troponin test on a patient with a chief complaint of “chest pain” or “heart problem.” The on-screen pop-up will facilitate use of the HEART Pathway CDS tool, by leveraging the normal work-flow of ED providers. For patients presenting with other symptoms that are concerning for ACS (ie, dyspnea, left arm pain, or jaw pain), providers will be encouraged to access the HEART Pathway tool manually. The HEART Pathway tool will be accessible from the EMR’s main menu (the ED Navigator).

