Once opened, by pop-up or manually, the HEART Pathway tool will prompt providers to answer a series of questions to determine eligibility and calculate a HEART score on eligible patients. The software will calculate a HEART score based on provider responses and give recommendations on further care based on the HEART Pathway (Figure 2). Patients with a low-risk HEART score (3 or less) and negative troponins at 0 and 3 hours will be identified as a population not requiring objective cardiac testing who can be discharged safely from the ED. Patients deemed at high-risk by the HEART Pathway or with a positive troponin (>99th percentile) will be identified for further testing and/or admission. HEART Pathway use will be tracked using weekly EMR reports. This report identifies all patients who meet inclusion criteria, determines whether the pop-up was activated, and whether the HEART Pathway tool was completed by the ED provider. Noncompliant providers, those that ignore the HEART Pathway pop-up, or those that fail to complete the HEART Pathway decision support tool assessment will receive notification and corrective education via email.

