### Data Collection

The effectiveness of the HEART Pathway will be assessed using electronic outcome surveillance. EMR data will be collected on all patients with chest pain. Insurance claims data will be collected on patients with Medicaid, MedCost, and BCBS of North Carolina. Data will include patient demographics, past medical history, cardiovascular risk factors, ECG results, troponin results, HEART score and HEART Pathway assessments, ED and discharge diagnoses, disposition, index visit length of stay, objective cardiac testing (stress testing or angiography) at the index visit or within 30 days, recurrent ED visits, readmissions, and myocardial infarction (MI) or death within the follow-up period. Data extraction from the EMR data warehouse (Clarity) will be automated and programmed to pull prespecified data points into our database on patients meeting eligibility criteria on a weekly or monthly basis (Figure 3). Electronic surveillance leverages our informatics strengths and data sharing relationships with insurers, to provide efficient and accurate outcome data. Data accuracy is enhanced by avoiding recall bias inherent in other follow-up methods such as telephone calls. Electronic surveillance also improves feasibility by allowing programmable follow-up on a large number of patients at a low cost. Inclusion of Medicaid patient claims should ensure that our data surveillance includes economically disadvantaged patients and is generalizable to the patient populations of other hospitals. Any discrepancies between sources of data will be adjudicated by study investigators blinded to patient pre- or post-intervention cohort participation. Based on prior studies, we expect 80% of patients to have follow-up data from the EMR or insurer claims. The Social Security Death Master File will be used to search for participants without follow-up data.

The preintervention cohort will be identified using the same inclusion criteria (aged ≥ 21 years with a complaint of chest pain and a troponin ordered without STEMI on ECG) for 1 year prior to integration of the HEART Pathway into cardiovascular care delivery at Wake Forest Baptist Health. The same data elements described above will be abstracted from the EMR and claims databases from BCBS, MedCost, and Medicaid.

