### Outcome Measures

Pre- and post-HEART Pathway cohorts will be compared for safety and health care utilization outcomes. The primary outcome will be hospitalization rate at 30 days for patients presenting with acute chest pain. Secondary outcomes will include index hospitalization rate, index and 30-day objective cardiac testing, hospital length of stay (LOS), recurrent ED visits, and nonindex admissions for chest pain. Outcomes will be assessed during the index visit and for 30 days thereafter.

Hospitalization will be defined as an inpatient admission or observation stay. Objective cardiac testing will be defined by any stress testing modality, coronary computed tomography angiography, or invasive coronary angiography. The modalities routinely available at Wake Forest Baptist Health include exercise ECG, exercise stress echocardiogram, dobutamine stress echocardiogram, coronary computed tomography angiography, stress nuclear imaging, stress cardiac magnetic resonance imaging, or invasive coronary angiography. LOS will be the time from ED arrival to hospital discharge for all patients, whether admitted or not. A recurrent visit to the ED will be defined as any patient revisiting the ED with chest pain or other symptoms suggestive of ACS within the 30-day follow-up period.

Safety outcomes will include death and acute MI within 30 days. Missed adverse events will be defined as death or MI occurring in patients discharged from the ED without objective cardiac testing. The definition of MI will be based on the Third Universal Definition of MI, which includes a rising or falling pattern of troponin with a cutoff representing the 99th percentile reference value with a coefficient of variation <10% [20].

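### Cohort entry depends on a troponin order, the same act that fires the pop-up in the post period, so a change in ordering at go-live could create or mask part of the effect on hospitalization

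*Protocol article*

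**What the plan says.** All places are in the Methods of the Protocol article.

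- Eligibility: adults "with acute chest pain, provider-ordered troponins, and without STEMI will be included". The same section describes the target population as patients in whom the provider suspects ACS, so the order stands in for that suspicion.
- HEART Pathway Implementation, on the trigger: "The modal window will appear when a provider has ordered a troponin test on a patient with a chief complaint". Two complaints qualify, chest pain and heart problem. The alert is a soft stop.
- HEART Pathway Implementation, on compliance: use is tracked weekly, and providers who ignore the pop-up or leave the tool unfinished "will receive notification and corrective education via email".
- Outcome Measures: "The primary outcome will be hospitalization rate at 30 days for patients presenting with acute chest pain". In the analysis the denominator is the eligible cohort.
- Data Collection, on the pre period: "The preintervention cohort will be identified using the same inclusion criteria".
- Data Collection, on scope: one sentence reads "EMR data will be collected on all patients with chest pain", but the automated extraction is set to "pull prespecified data points into our database on patients meeting eligibility criteria".
- Statistical Analyses: logistic regression with an intervention indicator, time, their interaction, and patient-level confounders, of which demographics, insurance and ACS risk factors are given as examples.

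The Limitations section (Discussion) names secular trends, provider maturation and loss to follow-up. It does not name selection through ordering.

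**The concern.** Membership of the cohort is decided by a provider's act, and the intervention attaches something to that act in one period only. A provider who has learned that an order brings an interrupting window, and possibly an email, may order fewer troponins in patients of very low risk. A provider who trusts the pathway to support early discharge may order more freely. In either case the written criteria stay the same while the patients who meet them change.

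The primary outcome is a proportion over those patients. Adding or removing patients who are rarely hospitalized moves that proportion even if every individual is managed as before. With the analysis as described, a reader could not separate such a shift from an effect of the pathway.

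**Working it through.** **Inputs from the article (Sample Size).** Expected pre-period hospitalization 53%; 5000 patients per period, 80% with follow-up, so 4000 per period; detectable reductions below 5% (read as percentage points) with 90% power at the two-sided 5% level.

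**Inputs that are assumptions.** x is the change in the number of low-risk patients given a troponin order, as a share of the original cohort. h is the hospitalization rate in those patients. The article gives neither, so both are varied.

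**Step 1. The plan's own figure.** For a pooled two-proportion comparison,

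n = [1.96·√(2·p̄·(1−p̄)) + 1.2816·√(p₁(1−p₁) + p₂(1−p₂))]² / d².

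With p₁ = 0.53 and n = 4000 this solves at d = 0.0362, or 3.6 points. Power for 53% against 48% is 0.994. The stated figure of under 5 points therefore reproduces, and 3.6 points is the benchmark used below.

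**Step 2. More low-risk orders, no true effect.** Post rate = (0.53 + x·h)/(1 + x). Example: (0.53 + 0.10 × 0.05)/1.10 = 0.535/1.10 = 48.6%. The last column is the probability of a significant result in an unadjusted test with 4000 pre and 4000·(1 + x) post.

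| x | h | Post rate | Shift (points) | P(significant) |
|---|---|---|---|---|
| 10% | 5% | 48.6% | −4.4 | 0.98 |
| 10% | 10% | 49.1% | −3.9 | 0.95 |
| 10% | 20% | 50.0% | −3.0 | 0.79 |
| 10% | 30% | 50.9% | −2.1 | 0.48 |
| 5% | 5% | 50.7% | −2.3 | 0.54 |
| 5% | 30% | 51.9% | −1.1 | 0.17 |

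**Step 3. Expansion that imitates the detectable difference.** Solving Step 2 for x gives x = d/(0.53 − d − h). With d = 0.0362:

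- h = 5%: 0.0362/0.4438 = 8.2%
- h = 10%: 0.0362/0.3938 = 9.2%
- h = 20%: 0.0362/0.2938 = 12.3%
- h = 30%: 0.0362/0.1938 = 18.7%

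**Step 4. Fewer low-risk orders, true 5-point fall.** Post rate = (0.48 − x·h)/(1 − x), with x = 10% of the cohort lost.

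- h = 5%: 0.475/0.90 = 52.8%, observed difference −0.2, power 0.04
- h = 10%: 0.470/0.90 = 52.2%, −0.8, power 0.10
- h = 20%: 0.460/0.90 = 51.1%, −1.9, power 0.38

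Without the loss, power would be 0.994.

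**Step 5. What the stated protections remove.**

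- Same written criteria: they do not help if the act that satisfies them changes.
- Three-month wash-in: removes a transition, not a lasting change.
- Time terms: remove a smooth trend that runs through both periods. A step at go-live loads onto the intervention indicator, and a drift that starts at go-live loads onto the interaction. Both are the effects being estimated.
- Covariates: remove the part of the case-mix shift they capture. The examples listed do not include clinical suspicion, on which ordering depends.

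**The case against.** The gate has a reason. The target population is patients in whom ACS is suspected, and a troponin order is a practical marker of that. All chest-pain visits is a different population, so replacing the primary cohort would change the question. This stands, and the primary cohort should be kept.

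The behavioural premise is unproven. Each pop-up follows its order and is a soft stop, so only learned behaviour could alter ordering. Routine serial testing adds a second troponin to patients already in the cohort; it does not by itself add patients. This also stands: direction and size are unknown.

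A reader might infer that covariate adjustment is powerless here. The article does not support that. Age and risk factors are two of the five HEART components, the confounder list is open, and past history and ECG results are collected. Adjustment should shrink the shift; it cannot be relied on to remove it.

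A reader might also infer that any plausible change in ordering matches the effect the study is sized for. The 5% scenarios (1.1 to 2.3 points) fall below the 3.6-point benchmark, the larger figures need a 10% change, all are unadjusted, and the article expects effects above its detectable difference.

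Finally, a condensed article may leave sensitivity analyses to an analysis plan. That is fair, and their absence is not the point. The point is what the article does fix: an eligibility gate that is also the trigger, and an extraction limited to patients who pass the gate. If the extraction stays so limited, no later plan could run the check from the study database.

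**Conclusion.** The structural overlap is explicit in the article, and the stated protections cover it only in part. Under assumed changes of 5% to 10% in low-risk ordering, the hospitalization rate moves by 1.1 to 4.4 points with no true effect, against a detectable difference of about 3.6 points. A 10% loss of low-risk orders reduces a true 5-point fall to between 0.2 and 1.9 points. These figures rest on assumed x and h, a 53% baseline, 4000 followed per period and no adjustment.

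The article does not show that ordering will change or that the primary result will be biased. It shows that, as described, the study could not tell. That justifies a measured check, not a different primary analysis.

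**What to change.** Keep the primary cohort and add two prespecified items.

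1. Report by month the proportion of adult ED chest-pain visits without STEMI that have a troponin order, and test for a level or slope change at implementation with the same time model as the primary analysis.
2. Add a sensitivity analysis of 30-day hospitalization in all adult chest-pain visits without STEMI, whether or not a troponin was ordered. Interpret the size of the primary effect in light of both.

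Attribution should not depend merely on the two hospitalization analyses agreeing in direction. With no true effect and spreading orders, the wider estimate would centre on zero and agree about half the time, and agreement in direction does not reveal an inflated size.

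Cost: the wider data are not clearly in hand. Data Collection speaks of all chest-pain patients but limits the automated pull to eligible ones, so the two statements need reconciling. The extraction must be widened for both periods, including STEMI exclusion and 30-day follow-up for visits without a troponin. The effect will be diluted in the wider denominator, so a smaller estimate there is expected and is not in itself evidence against the pathway.

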### Study Timeline

Pre- and post-HEART Pathway ADP implementation cohorts will each accrue patients with acute chest pain for 1 year, with a 3-month wash-in period (Figure 1). Data will be collected electronically from all patients using health system electronic medical records (EMRs), and claims data from insurers will be used on a subset of patients insured by Blue Cross Blue Shield (BCBS) of North Carolina (the largest insurer in the state), MedCost, or North Carolina Medicaid.

**Figure 1 figure1:**

HEART Pathway Implementation prospective cohort design.

### HEART Pathway Implementation

The HEART Pathway intervention will incorporate elements of the Chronic Care Model framework (decision support and clinical information systems) by providing test ordering and disposition decision support to ED practitioners and personalized care planning for patients with acute chest pain [8,18,19]. This intervention uses a clinical decision aid (the HEART score; Table 1) [13-15], with 2 serial troponin measurements obtained at 0 and 3 hours after ED presentation. The HEART Pathway algorithm (Figure 2) will be integrated into the EMR system, EPIC (Madison, WI, USA), as an interactive CDS tool. A model window (on-screen pop-up) will display the HEART Pathway tool as a Best Practice Advisory when clinically indicated. The child window will require interaction before the user may return to the parent window in the EMR, but will not force the user to utilize the HEART Pathway tool (the alert will be presented as a *soft-stop*). The modal window will appear when a provider has ordered a troponin test on a patient with a chief complaint of “chest pain” or “heart problem.” The on-screen pop-up will facilitate use of the HEART Pathway CDS tool, by leveraging the normal work-flow of ED providers. For patients presenting with other symptoms that are concerning for ACS (ie, dyspnea, left arm pain, or jaw pain), providers will be encouraged to access the HEART Pathway tool manually. The HEART Pathway tool will be accessible from the EMR’s main menu (the ED Navigator).

Once opened, by pop-up or manually, the HEART Pathway tool will prompt providers to answer a series of questions to determine eligibility and calculate a HEART score on eligible patients. The software will calculate a HEART score based on provider responses and give recommendations on further care based on the HEART Pathway (Figure 2). Patients with a low-risk HEART score (3 or less) and negative troponins at 0 and 3 hours will be identified as a population not requiring objective cardiac testing who can be discharged safely from the ED. Patients deemed at high-risk by the HEART Pathway or with a positive troponin (>99th percentile) will be identified for further testing and/or admission. HEART Pathway use will be tracked using weekly EMR reports. This report identifies all patients who meet inclusion criteria, determines whether the pop-up was activated, and whether the HEART Pathway tool was completed by the ED provider. Noncompliant providers, those that ignore the HEART Pathway pop-up, or those that fail to complete the HEART Pathway decision support tool assessment will receive notification and corrective education via email.

